## 2. Aims

To address these gaps in knowledge, we conceptualized this parallel-group randomized control trial (RCT) to investigate the effects of a mindfulness intervention. We named it the Mindfulness Awareness Program (MAP), with community-dwelling Asian older adults clinically diagnosed with mild cognitive impairment, examining comprehensive outcome measures. We aimed to determine the effects of MAP compared to a Health Education Program (HEP), the active control arm, on (1) delaying or reversing cognitive decline amongst older adults diagnosed with MCI, (2) neuroimaging and comprehensive peripheral biomarkers associated with MCI, and (3) affective symptoms, namely depressive and anxiety symptoms, and physical functioning measures.

## 3. Methods and Design

### 3.1. Study Design and Setting

This trial is a parallel-arm and single-blinded RCT, which aimed to evaluate the effects of MAP over 9 months. The control arm partook in the HEP. The study protocol had been prospectively approved by the National University of Singapore Institutional Review Board (NUS IRB-Reference Code: B-14-110), and *a priori* registered at ClinicalTrials.gov (NCT02286791), a service of the United States National Institute of Health. We recruited our study participants from a larger on-going study, DaHA based at TaRA@JP [41]. It is a community-based research center established by the NUS Psychological Medicine department and located in a shopping mall, in the western part of Singapore. The primary recruitment strategy was through home visits to the government-built flats in public housing blocks located next to the study center. DaHA aimed to recruit older adults aged 60 and above. Once potential participants expressed interest to participate in the study, they were invited to the study center for informed consent taking, followed by detailed interviews and assessments. Dementia incidence was 4.6% at recruitment [42].

### 3.2. Study Participants—Eligibility Criteria

The study was conducted in accordance with the Declaration of Helsinki. As shown in Figure 1, the participants were recruited from the Diet and Healthy Ageing Study (DaHA) (NUS-IRB Reference No:10-517) [41], a longitudinal cohort study based at the Training and Research Academy at Jurong Point (TaRA@JP). The research nurses, research assistants, and [name] obtained written informed consent from the potential participants before screening for potentially eligible participants. All potential participants were screened for cognitive status and other eligibility criteria based on *a priori* inclusion and exclusion criteria.

The inclusion criteria were:(1)Community-dwelling older adults aged between 60 and 85 years old and fulfilled the Peterson’s operational criteria of mild cognitive impairment [42]:
At least one age-education adjusted neurocognitive test Z-score < −1.5;Do not meet DSM-IV criteria for major neurocognitive disorder;Memory/cognitive complaint, corroborated by a reliable informant;Intact activities of daily living.
(2)Function independently.(3)Able to travel on their own to TaRA@JP and participate in the study.(4)Does not have a diagnosis of dementia.

The exclusion criteria were:(1)Dementia or normal ageing;(2)Diagnosed with a neurological condition (e.g., epilepsy, Parkinson’s disease);(3)Diagnosed with major psychiatric condition (e.g., major depressive disorder);(4)Suffer from a terminal illness (e.g., cancer);(5)Had significant visual or hearing impairment;(6)Had marked upper and lower limb motor difficulties, which may affect their ability to participate in the study;(7)Participation in another interventional study concurrently.

It is noteworthy that we did not exclude participants who did not consent to provide bio-specimen or MRI scans. In such cases, we continued with collecting all other measures to which the participants have consented, including interventions and neurocognitive outcome assessments. All participants were also newly-diagnosed community-dwelling MCI participants, who were naïve for medications targeting cognitive impairment at the start of the study.

### 3.3. Clinical Diagnostic Procedure for MCI

To derive the cognitive status of the participants, there was a two-step procedure. First, the assessors, comprised of a team of trained and certified research assistants and [name], administered the clinical dementia rating (CDR) scale and neurocognitive assessments to all screened participants at the research center and derived preliminary research diagnoses. Subsequently, final research diagnoses of MCI were made during the study’s consensus meetings by a panel consisting of at least two senior consultant-ranked psychiatrists ([name] and [name]) and a clinical scientist ([name]).

### 3.4. Recruitment and Baseline Procedures

The participant flow from recruitment through to the end of study is shown in Figure 1 and Figure 2. Following the successful screening, baseline assessments were administered to all participants by trained research nurses and research assistants. The participants will then be randomized into one of the two study arms.

### 3.5. Randomization Procedure

After completing informed consent, screening, and baseline assessments, eligible participants were then randomized by an independent research assistant who was not affiliated with the trial. Using a random number generator function on the Random Allocation Software version 2.0 (Saghaei, Isfahan, Iran), the research assistant randomly allocated the participants in a 1:1 ratio to either the MAP or the HEP arm. The study’s research coordinator, [name], then assigned the participants to the intervention arms. A single-blind design was employed; the assessors were blinded to the study arm assignments while the participants were aware of the study arms they were assigned to.

### 3.6. Delivery of Interventions

Since this is a parallel-arm RCT, the interventions for the two arms were conducted concurrently, at the same time of the same day and different rooms at the same research center. For the first three months, we held weekly intervention sessions for both arms, with each session of the MAP and HEP lasting approximately 1 h. For the study follow-up period, i.e., from 3-month to 9-month, 6 monthly booster sessions were held for both study arms. We recorded the attendance throughout the intervention period till the end of the 9-month period. We also provided the participants with personal diaries to record their practices at home. They were asked to return their session-specific diaries at the subsequent sessions to enable us to determine intervention adherence to daily practice and the frequencies of the practice. The sessions in each arm were structured with themes, led by the trainers with relevant experience and expertise.

### 3.7. Active Treatment Arm—Mindfulness Awareness Practice (MAP)

The treatment arm performed MAP, which was designed to foster awareness of internal states and promote positive mental and physical health through mindful awareness practices. MAP is a Singaporean version of the mindfulness intervention [43], modeled on the didactics of McBee mindfulness-based elder care (MBEC) [44], which adapted the mindfulness techniques to the unique needs of the older adult population [44]. We employed MBEC instead of mindfulness-based stress reduction (MBSR) due to several reasons; MBSR practices target the general population without focusing on the specific needs of older adults, including assuming that participants have good attention spans to understand and follow instructions and can commit to the practices and participate in simple exercises. However, older adults are often not able to follow many practices of the MBSR due to these requirements [45]. Thus, while maintaining the core intention of mindfulness, MBEC made adaptations to the MBSR model, making it tailored and uniquely suitable for older adults [45]. Each session was led by a certified and experienced instructor with years of experience teaching MAP techniques with the older adults. The various mindfulness techniques employed included:
(1)Mindfulness of the senses practice, which is to attend to the different senses (i.e., vision, hearing, touch) to cultivate focused attention. For example, the participants were requested to pay attention to their bodily senses while performing daily activities, including brushing their teeth.(2)Mindful breathing with the body scan practice, where in a sitting position, participants were guided to develop kinesthesia by focusing their attention on various parts of their body as a relaxation technique. In more detail, the participants were guided by the instructor to place their attention on one part of their body at a time, while imagining directing their breath to the respective areas of their body and subsequently relaxing muscles at the specific areas. This practice was repeated, focusing on different body parts, starting from the toes to the head and vice versa.(3)Movement nature meant a practice where participants were taught to move with awareness for flexibility, strength, and confidence. It was based on the Feldenkrais method aiming to restore natural coordination and movement mobility, incorporating two of the cornerstones of the Feldenkrais method, namely “Awareness Through Movement”^®^ and breathing awareness [46].(4)Visuomotor coordination tasks, which trained the participants in mind-body coordination. The participants were guided to perform different cognitively demanding tasks requiring the fine coordination of the visual and motor systems. For example, the participants used one hand to perform a task with rubber bands and then switched quickly to performing the same task using the other hand, back and forth to be repeated a few times.(5)Lastly, mindful stretching aimed to relax the muscles, by requiring the participants to stand up and stretch their muscles mindfully, while sighing and releasing the tensions felt in the muscles.

Figure 3a,b shows the pictures of the participants practicing the mindfulness practice during the intervention sessions.

### 3.8. Active Control Arm—Health Education Program (HEP)

Modeled on the HEP proposed by MacCoon et al. [47], the active comparator group participated in a series of talks on health-related topics of interest to older adults. The weekly topics covered hypertension, diabetes, dementia, depression, medications, exercise, diet, sleep, home safety, falls and social support. The monthly sessions reviewed the topics and discussed how the participants had implemented healthy practices in their daily lives. Due to the breadth of the topics covered, the program was delivered by a panel of healthcare professionals specialized in the topics, which included clinicians, nurses, and psychologists. It was recommended to employ health education as the active control arm in mind-body intervention, to control for components that are non-intervention-specific [48].

### 3.9. Data Management

The trial coordinator monitored the screening and recruitment procedures to ensure the informed consent process was being properly conducted and obtained prior to the start of the study, in line with the institutional IRB. Upon successful screening, informed consent and enrollment, each participant was assigned a unique numerical study number with all the subsequent documents and sample labeling using the same study number. Only the Principal Investigator ([name]) and the study coordinator have access to the identifiers. Data (Table 1) were entered and stored on a standard desktop computer with password protection. Following the NUS data management policy (DPRT-2011-04), all data were prospectively kept for ten years, beyond which they will be destroyed. Data entry and processing procedures ensured that the blinding was maintained during the entire course of trial. A backup system was in place; apart from the files stored at the desktop at the research center, i.e., TaRA@JP, another copy of all the files were stored in an external hard drive.

Two databases were created: (1) an administrative database, a Microsoft Excel spreadsheet to compile data related to administrative matters and documentation process. They included participant identification data, administrative data, and regulatory data, and (2) research database, which included a compilation of data that were used for documenting outcome measures and statistical analyses. For both databases, they were secured and encrypted with password protection, with access granted only to the Principal Investigator, the study coordinator, and a data entry staff member. The primary and secondary measures were independently reviewed by a research assistant to ensure correct data entry.

Any hardcopy data collection forms transferred from TaRA@JP to the office at National University Health System were sent via courier or registered post, or transported by taxi or private transport, to minimize the risk of data loss. The consent forms and data collection forms were stored in a locked cabinet at TaRA@JP, and access to them was only made available by the Principal Investigator or the study coordinator.

### 3.10. Statistical Analysis

Based on previous studies [35,49,50,51] examining the effects of mindfulness on the means and SDs for co-primary outcomes chosen for this study, i.e., fluid biomarkers and neurocognitive tests, we estimated the effect sizes to be 0.5. Hence, we required 24 participants in each group to have a power of 80% to detect statistical significance at 5% level. Considering a potential 20% drop-out rate, 30 participants needed to be assigned to each group at baseline. Hence, the targeted total sample size was 60.

All demographic and outcome measures were expressed as mean ± standard deviation (SD). We used either Fisher’s exact, Student’s or chi-square *t*-test to examine the differences in the baseline variables, as per the nature of the data. In the event the raw values of the measures were not conforming to the normality assumption, the raw values were natural log-transformed for subsequent analyses. Successful normalizations were based on dot plots, skewness, and kurtosis.

We employed the linear-mixed model to examine the treatment effects of MAP on the biomarkers and psychometric scale outcome measures, compared to the active control group, HEP, over the three time-points. For the psychometric and fluid biomarker measures, we performed intention-to-treat analyses using linear-mixed model, because it is robust to missing data. The model considers all the participants included in the baseline, regardless of whether they have missing values at subsequent follow-ups [52]. For the neuroimaging measures, since the drop-out rates were much higher, we used per-protocol analyses, where only participants that completed the intervention and had neurocognitive and neuroimaging scans at follow-ups were included in the ANOVA analyses.

In each of the linear-mixed models, we entered the outcome measure of interest as the dependent variable. The time-points of the intervention, treatment arm, and an interaction term between time-points and treatment arm were treated as the independent variables. Covariates for all the models included the baseline values of the respective outcome variable, age, sex, and years of formal education. We also collected measures for other covariates relevant to MCI and dementia, including the geriatric depression scale (GDS) and geriatric anxiety inventory (GAI) clinical cut-offs, history of cardiovascular diseases, and history of myocardial infarction. These additional covariates were explored to examine their effects on the basic models, using the model fit statistics, namely the Akaike information criterion (AIC) and Bayesian information criterion (BIC) values. In the final models, for the additional covariates, only the significant ones for each model were retained. We based all the analyses on the intention-to-treat principle, hence all the participants who had measures at at least one time-point were included in the analysis. All statistical analyses were and will be further performed using the Statistical Package for the Social Sciences (SPSS) Statistics for Windows, version 23.0 (IBM Corp., Armonk, NY, USA). A two-tailed *p*-value of < 0.05 was and will be considered statistically significant.

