Several implementation outcomes are worth noting. First, the study fell short of the targeted 60 participants and recruited 55 participants instead. Coupled with the higher-than-expected drop-out rates, the power of the trial was lower than the calculated 80%. In this parallel-group trial, the participants in the HEP group attended the intervention at the same time and same day throughout the intervention period as MAP, but separately and in different rooms at our research center. Hence, there were minimal interactions. However, we acknowledged that there was still plausible inadvertent contamination due to the participants conversing and interacting before and after their respective intervention sessions. One mitigation was that we let the participants in the MAP arm leave the intervention site, i.e., our research center, earlier than the HEP participants, minimizing the contamination. The registration booths were also separate for the two groups. The recruitment rate, 43.65% (55 recruited out of 126 screened), is lower than another RCT targeting participants with MCI, 66.81% [59]. Conversely, the attendance and retention rates were approximately 88 and 89%. These figures are very similar to other psychosocial interventions targeting MCI, which are approximately 90 and 85%, respectively [20,60]. We strengthened follow-ups and adherence and minimized potential drop-outs by having the study’s coordinator and research assistants conduct weekly reminder calls to the participants or family members three days prior to each intervention session. Since our target sample population had cognitive impairments, these regular reminder calls could have ensured high adherence rates to the interventions. The instructors played a critical role in both the MAP and HEP. Compared to conducting interventions on cognitively intact older adults, enhanced instructors’ interaction was needed to effectively and continuously engage this population. Enhanced interaction with the instructors might explain the high attendance rate as well. We were unable to accurately determine the adherence rates of the interventions. Although we provided homework and personal diaries to the participants at the end of each session, the participants often did not bring their personal diaries back to the research center for fidelity check purpose. Based on the feedback from the instructors and our interaction with the participants, we suspect that due to having MCI, many participants did not perform the home practices assigned. For future studies, due to the on-going COVID-19 pandemic, one future direction is to use mobile health technology, while considering the electronic literacy of older adults. Other implementation strategies could be found in our previous paper [61]. The lost to follow-up rates for fluid biomarkers and neurocognitive tests were very similar, although for the neuroimaging measures, the rates were high in both the MAP and HEP groups. By delineating the implementation outcomes and lessons learned from this pilot mindfulness trial with MCI, we hope they will serve as a guide for future study design and implementations. Lastly, no adverse events related to either the MAP or HEP intervention was reported, suggesting the feasibility and safety of the interventions.

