
This trial has several limitations. Despite the encouraging findings, this is a proof-of-concept study. With encouraging findings, future validation in larger RCTs is needed. Blinding of the participants to the assigned interventions was not feasible. One potential mitigation is to use sham meditation as the active control arm [37]. Due to limitations in logistics and human resources, only a single time-point sample of saliva samples were collected for each participant at each time-point. Thus, the findings for salivary cortisol levels reported should be interpreted with caution. For higher accuracy and reliability, the ideal saliva sampling method is to collect saliva samples at multiple time-points throughout the day and take the reading from the area under the curve or the concentration versus time curve with respect to zero [62]. Lastly, the absence of significant *p*-values for several outcome measures might have been attributed to the study’s slightly reduced power, as the original recruitment target was not met.

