Despite the limitations, this study represents a significant advancement on several fronts. First, we employed an RCT design, with the active control arm controlled for several intervention components, which were not specific to mindfulness. Adding the active control group proposed by MacCoon et al. (2012) [47] thus considerably improved the study’s conclusions on effectiveness. This RCT included equal instructor’s attention for both intervention groups [37], and interventions were conducted at the same time of the day and on the same day of the week [23], and had equal length of the sessions [37]. This study design minimized residual confounding effects, by ensuring that the two study arms differed mainly in the interventions being compared [63]; this is the first RCT to concomitantly and comprehensively examine a range of psychometric scales and biomarkers representing different biological mechanisms, allowing us to pinpoint the specific effects of MAP in MCI, and contributing to filling the dearth of knowledge of mindfulness intervention on biomarkers in MCI. This study also addressed one of the main limitations present in the mindfulness intervention literature, i.e., the 8-week short follow-up period, by the addition of monthly booster sessions from 3- to 9-month. Lastly, to our knowledge, although with moderate power, compared to previous two RCTs conducted with MCI (N = 14) [20,21], this study is to date the largest and longest follow-up RCT of mindfulness intervention conducted with older adults diagnosed with MCI. With this extended follow-up period, we elucidated the long-term effects of mindfulness, contributing to expanding the knowledge on this topic.

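### The sample size in section 3.10 does not follow from its stated inputs: 24 per group at an effect size of 0.5 gives about 40% power, not 80%, unless a correlation the article does not state was assumed

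*Protocol article*

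**What the plan says.** Section 3.10 (Statistical Analysis) of the protocol article bases its effect size on earlier studies "examining the effects of mindfulness on the means and SDs for co-primary outcomes chosen for this study", and reports that "we estimated the effect sizes to be 0.5". From this it concludes that "we required 24 participants in each group to have a power of 80% to detect statistical significance at 5% level". It then allows for 20% drop-out, giving 30 per group and 60 in total. Section 3.10 also fixes a two-tailed 5% threshold, and section 3.5 fixes 1:1 allocation.

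The planned analysis is a linear mixed model over three time-points with a time-by-arm interaction, adjusted for the baseline value of the outcome, age, sex and education. No correlation between visits, variance reduction or target contrast is given.

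Two statements in section 5 (Discussion) rely on the calculation. The paragraph on implementation outcomes says that "the power of the trial was lower than the calculated 80" per cent, citing both the recruitment shortfall (55 rather than 60) and higher drop-out than expected. The limitations paragraph suggests that the absence of significant p-values for several outcomes may be due to "slightly reduced power, as the original recruitment target was not met".

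**The concern.** An effect size built from means and SDs for a two-arm comparison is most naturally a standardised mean difference. At 0.5, 24 per group is far below the size that a two-sided 5% test needs for 80% power, and the article presents the 24 as following directly from the 0.5. This is a printed figure that does not reproduce. It is not a detail left to a fuller document.

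The stake is interpretation. If 80% is taken as the starting point, a non-significant result looks like a small accident of recruitment. If power on the stated inputs was about 40% from the outset, recruitment explains very little, and an effect of the assumed size was more likely than not to be missed by the simple comparison.

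**Working it through.** **Inputs, all from the article.** Effect size d = 0.5, 24 per group, 80% power, 5% level, two-tailed, 20% drop-out (section 3.10). Allocation 1:1 (section 3.5). Randomised 28 v 27 (Table 2). Lost at 9 months for psychometric measures: 10 of 28 and 8 of 27 (section 4.3), leaving 18 v 19.

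**Drop-out step.** 24 / (1 − 0.20) = 30 per group, 60 in total. This reproduces, so the fault lies in the 24.

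**Sample size for 80% power.** Normal approximation: n per group = 2(1.960 + 0.842)² / 0.5² = 62.8, so 63. The exact t calculation gives 63.8, so 64. The stated 24 does not reproduce.

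**Power at given group sizes.** Noncentrality = d × √(n₁n₂/(n₁+n₂)), referred to the noncentral t on n₁+n₂−2 degrees of freedom.

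| Groups | Noncentrality | Power at d = 0.5 |
|---|---|---|
| 24 v 24 (as planned) | 0.5 × √12 = 1.73 | 39.6% |
| 30 v 30 (no drop-out) | 0.5 × √15 = 1.94 | 47.8% |
| 28 v 27 (randomised) | 1.85 | 44.4% |
| 18 v 19 (9-month psychometric) | 1.52 | 31.5% |

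With 24 per group, 80% power corresponds to d = 0.83.

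**Other readings tried.**
- One-sided 5%: 51 per group needed, and 24 gives 52%. The two-tailed threshold excludes this in any case.
- 0.5 read as Cohen's f (d = 1): 17 per group needed, and 24 gives 92%.
- Paired or one-sample t at 0.5: 34 needed. This is not a between-arm comparison.

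None gives 24 per group at 80%.

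**Allowing for baseline adjustment.** The article states no correlation, so r below is my assumption, taken as equal between all pairs of visits. The effective effect size is d/√(1 − r²) for ANCOVA at one follow-up, and d/√((1 + r)/2 − r²) for the baseline-adjusted mean of two follow-ups.

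| r | Contrast | Variance factor | Effective d | Power, 24 v 24 | Power, 18 v 19 |
|---|---|---|---|---|---|
| 0.5 | One follow-up | 0.75 | 0.577 | 50% | 40% |
| 0.7 | One follow-up | 0.51 | 0.700 | 66% | 54% |
| 0.5 | Mean of two | 0.50 | 0.707 | 67% | 55% |
| 0.7 | Mean of two | 0.36 | 0.833 | 81% | 69% |

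At 24 per group, 80% is reached at r of about 0.80 for one follow-up and about 0.69 for the mean of two.

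**How much does the recruitment shortfall explain?** Unadjusted, going from 30 v 30 to 28 v 27 moves power from 47.8% to 44.4%, about 3 points. The gap between the claimed 80% and 39.6% at 24 per group is about 40 points.

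**The case against.** The planned analysis is not a t-test. It is a baseline-adjusted mixed model over three time-points, and the section names neither the effect-size metric nor the test behind the 24. A journal article may omit an assumed correlation that the full protocol contains, and at r of about 0.7 the mean of two follow-ups does reach 80%. A repeated-measures interaction calculation with f = 0.25, three time-points and 48 participants also gives about 80% at r = 0.1. These points stand as possible origins of the 24. They do not validate the text: the article derives the 24 from 0.5 alone, states no f, r or averaged contrast, and an interaction of f = 0.25 is a larger contrast than a between-arm difference of 0.5.

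Four stronger readings are tempting, and the article does not support them.
- A reader might infer that the trial could never have had 80% power. The adjusted model could have reached it under a high enough correlation.
- A reader might infer that attained power at 9 months was simply 32%. That is an unadjusted complete-case figure, whereas the planned model adjusts for baseline and keeps participants with at least one measurement.
- A reader might infer that null results say nothing. An interval around a null estimate still carries information, and the limitations already call the trial proof-of-concept.
- A reader might count "although with moderate power" in the Discussion as the same error. It is a loose comparison with two trials of 14 participants and makes no numerical claim.

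In fairness, the implementation paragraph concedes lower power and names drop-out as well as recruitment. Only the limitations sentence rests on recruitment alone.

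**Conclusion.** The calculation is wrong as written. On the stated inputs, 24 per group has about 40% power at 0.5, against the 80% claimed. This rests on reading 0.5 as a standardised mean difference in a two-arm, two-sided 5% comparison with no gain from covariates or repeated measures, which is the only reading the stated inputs support. No allowance is made for multiple co-primary outcomes. The gap closes only under a correlation of about 0.7 to 0.8, depending on the contrast, which the article does not give. The two Discussion statements inherit the 80%, and the recruitment shortfall accounts for only about 3 points.

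**What to change.** In section 3.10, do one of two things. Either restate the power as about 40% at 0.5 with 24 per group, with a detectable difference of about 0.83 at 80% power; or state the correlation and the contrast actually assumed, with the resulting power.

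In section 5, stop using 80% as the starting point in the implementation paragraph, and stop attributing absent significance to slightly reduced power from missed recruitment in the limitations paragraph. If power at the 9-month psychometric numbers is quoted, give it as a range labelled by assumption: about 32% unadjusted; 40% and 54% for one-visit ANCOVA at correlations of 0.5 and 0.7; 55% and 69% for the baseline-adjusted mean of two follow-ups at the same correlations. Interpret non-significant results through 95% confidence intervals.

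This changes text only and needs no extra enrolment. The cost is a less favourable stated power, unless the missing assumption can be documented.
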